## Methods

### Design

The present protocol is based on reporting guidelines from the SPIRIT guideline for Standard Protocol Items for Clinical Trials [45] adapted as recommended when reporting protocols of feasibility trials [46]. The study is designed in order to inform and evaluate the feasibility of a possible future, full-scale RCT of MCA versus AAU. We will evaluate the feasibility of the interventions in terms of clinician resources and patient’s acceptability and adherence to the intervention and comparator, selected based on recommendations for the conduct of feasibility trials [47–49].

In addition to these feasibility outcomes, we will assess outcomes regarding readiness for change, symptoms, and regarding self-esteem and self-efficacy. Data are gathered from patients through a number of questionnaires delivered by the RedCap © webmodule prior to randomization (T0), at the end of MCA (T1) and after 4 weeks of psychotherapy (T2)—the absolute time depends on clinical logistics and timing of group therapy onset.

### Trial design

A two-armed, parallel randomized controlled feasibility and superiority trial comparing the effect of pre-treatment MCA with AAU.

A CONSORT diagram is provided in Fig. 1. A diagram of the proposed study and the outcome assessment is provided in Fig. 2. The trial data collection and randomization, stratified by gender, will be carried out in the web-based data management system REDCap (https://www.project-redcap.org/). Self-ratings will also be collected on the web-based REDCap platform.

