## Background

### Introduction and rationale

Anxiety disorders represent an important public health concern in the Western world [1, 2]. Estimates from a large European epidemiological survey suggest that 14% of the European population will meet the criteria for an anxiety disorder within their lifetime [3]. These disorders are often associated with a chronic, debilitating course for the affected individual as well as high socio-economic costs [4–6]. Anxiety disorders are among the leading causes of the global disease burden and the annual costs in Europe alone reached 74 billion Euros in 2010 [7, 8]. Continuous efforts to improve treatment programs for anxiety pathology are imperative.

Social phobia (SP) is the most common among the anxiety disorders. The fear of being observed or negatively evaluated by other people is a prominent characteristic of individuals with social phobia. This fear leads the individual to avoid performance or social situations (e.g., speaking or eating in front of others, making acquaintances, and meeting authorities), or enter such situations with substantial discomfort [9]. This evasiveness severely impacts the social functioning and quality of life of affected individuals [10, 11].

Similarly, avoidant personality disorder (AvPD) is characterized by a pervasive pattern of social inhibition, feelings of inadequacy, and hypersensitivity to negative evaluation, which result in marked evasiveness and avoidance of social interactions. AvPD patients perceive themselves as unwanted and isolated from others [9]. The Diagnostic and Statistical Manual of Mental Disorders, fifth edition (DSM-5) [12], recognizes a considerable overlap between AvPD and SP. Although the relationship between the disorders is a matter of debate [13], the dominant conceptualization is that the two disorders represent a spectrum, differing from each other only in severity (the severity continuum hypothesis [14]). In the upcoming revision of the International Classification of Diseases, tenth edition (ICD-10), AvPD will be removed as an independent diagnosis [15], which further supports the severity continuum hypothesis. Similar to the anxiety disorders, AvPD is associated with profound impairment in daily life for the affected individual, as well as high socio-economic costs [16]. Hence, the present study protocol relevantly focuses on SP and social evasiveness.

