Danish outpatient mental health services provide time-restricted, standardized, interdisciplinary treatment programs for social phobia and AvPD. Following national clinical practice guidelines, the treatment programs offer evidence-based cognitive-behavioral therapy for social phobia and mentalization-based therapy for AvPD.

The content and format in the standardized treatment programs for moderate-severe SP and AvPD are regulated in accordance with the Danish Health Authority guidelines. The treatment program for SP consists of diagnostic assessment (1–3 consultations), medical consultations (1–2 consultation), and group therapy with two therapists (14 sessions (120 min)), relatives’ support (1 session), and network consultation (1 session) [17]. Correspondingly, the standardized outpatient treatment program for AvPD includes up to 78 h of clinician time consisting of clinical assessment (2 h), medical consultations (1–2 consultations), group therapy with two therapists (30 sessions (120 min)), and network consultation (1–2 sessions) [18].

However, despite a solid evidence base for the efficacy of cognitive-behavioral therapy for social phobia, recent meta-analytic data suggest that only 45% of patients suffering from social phobia remit from their principal diagnosis after treatment and patients with social phobia have a worse outcome than patients with other anxiety disorders [19]. The evidence-based psychological treatment for avoidant personality is limited in terms of number and quality of studies and the remission rates vary substantially from 40 to 80% [20].

Data from a recently finalized multicenter randomized controlled trial [21] investigating the relative efficacy of group diagnosis-specific versus transdiagnostic cognitive-behavioral therapy for anxiety disorders or depression supports the meta-analytic findings on social phobia. In this trial, 291 patients with anxiety disorders or depression received standardized treatment programs from three Danish mental health services, and the results suggested that only half of the patients no longer met diagnostic criteria for their principal diagnosis by the end of treatment [22]. No data exists on the efficacy of the standardized programs for AvPD.

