### Participants and eligibility criteria

We aim to include 42 patients who satisfy the inclusion criteria: (1) a patient with a tentative ICD-10 diagnosis of either SP or AvPD, (2) who is going to be offered treatment in the aforementioned clinics, (3) is 18–65 years of age, (4) has given written consent to participate, and (5) has sufficient knowledge of the Danish language.

Patients will be excluded if (1) the risk of suicide is high or moderate according to the investigator, (2) they have alcohol or drug dependency, and (3) they have a co-occurring eating disorder with BMI < 18 or psychotic illness.

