### Randomization and blinding

Patients will be randomized 1:1 to either the MCA or AAU on an individual level. Allocation to experimental intervention or comparison intervention will be computer-generated using the software REDCap © [50].

Due to the nature of the intervention, neither participants nor the researcher who will administer the intervention can be blinded to allocation. However, data will be re-coded for concealment and analyzed without access to information about allocation. The conclusion will be written prior to unblinding.

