#### Statistical considerations

As the primary objective of the present trial is to test feasibility, a formal power calculation is not required. However, the present trial also wishes to examine MCA versus AAU, and we present the following power calculation for the primary outcome: readiness for change. Sample size calculation is based on figures in Dozois et al. [71] of patients with panic/anxiety, where the primary outcome “Contemplation stage score” in readiness for change was mean 37.3 (SD 1.9) for CBT responders and mean 34.4 (std 3.4) for non-responders, i.e., with significance level 5% and power 90%. This yields a total sample of 36 with 18 patients in each arm. We strive for 42 patients to account for attrition around 15%. We find it feasible to include the 42 patients since 64 patients are offered treatment packages annually (40 SP and 24 AvPD).

A detailed statistical analysis plan will be published on ClinicalTrials.gov prior to data processing initiation. Briefly, we expect to report descriptive data such as data for the feasibility criterion as percentages, means, and variation as standard deviation. Outcomes will be analyzed as continuous and categorical measures (i.e., responder status and new diagnosis, see below). All statistical analyses will be performed as intention-to-treat analyses (ITT); however, main outcomes will also be analyzed for completers only for sensitivity reasons. Missing data will be handled by the use of multiple imputations. The pre- to post-treatment effects of the MCU or AAU will be determined utilizing a series of repeated measures analyses of variance (rmANOVAs). Analysis will be based on masked data (recoded data for concealment of allocation). Conclusions of the main outcomes will be formulated prior to unmasking the data. Statistical calculations will be performed prior to unblinding. All statistical calculations will be performed in R and RStudio [72].

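### Allocation is stratified by gender alone although the trial pools SP and AvPD; entry diagnosis should enter the models in a form that can act on change, mainly for the T2 outcomes

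*Protocol article*

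**What the plan says.** Under Participants and eligibility criteria, the first inclusion criterion admits "a patient with a tentative ICD-10 diagnosis of either SP or AvPD". The Introduction and rationale calls the relationship between the two disorders debated, but reports that "the dominant conceptualization is that the two disorders represent a spectrum, differing from each other only in severity". The same section describes separate programmes: "evidence-based cognitive-behavioral therapy for social phobia and mentalization-based therapy for AvPD", with 14 group sessions for SP and 30 for AvPD, each of 120 minutes.

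On allocation, Randomization and blinding says "Patients will be randomized 1:1 to either the MCA or AAU on an individual level", and Trial design adds "The trial data collection and randomization, stratified by gender, will be carried out in the web-based data management system REDCap". Gender is the only factor named. According to Recruitment, the clinical diagnosis is set at the first consultation, before consent, so it is known when the patient is randomised.

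Statistical considerations outlines intention-to-treat analysis, multiple imputation and repeated-measures ANOVA of pre-to-post effects. It names no diagnosis term and leaves the detail to a SAP to be published before data processing. Table 1 has LSAS, RSES and GSES at T0, T1 and T2, and URICA at T0 and T1 only. The text following the instrument list places psychotherapy after the primary endpoint.

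**The concern.** Of the features the article describes, entry diagnosis is the one that separates these patients by severity and by later therapy. It is available before allocation but plays no part in it. The factor that is used, gender, is not linked anywhere in the article to readiness, symptoms or programme.

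With about 21 patients per arm, chance can leave one arm with clearly more AvPD patients. If SP and AvPD patients change differently between T0 and T2, part of the arm difference would then reflect diagnosis and type of therapy. Attendance in the first weeks of group therapy is exposed in the same way, and it has no baseline score to absorb a difference. The Discussion intends to use the trial's effect sizes to plan a larger trial, so an imbalance in this one small sample could be carried forward.

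**Working it through.** **1. The plan's own sample size.** Inputs from Statistical considerations: means 37.3 (SD 1.9) and 34.4 (SD 3.4), 5% significance, 90% power; two-sided is assumed.

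- Difference 37.3 − 34.4 = 2.9. Pooled SD = √((1.9² + 3.4²)/2) = 2.754.
- n per arm = 2 × (1.960 + 1.282)² × 2.754² / 2.9² ≈ 18.95, so 19 per arm and 38 in total. With the simple mean of the two SDs, (1.9 + 3.4)/2 = 2.65, n is 18 per arm, which is the stated 36.
- 36 × 1.15 = 41.4, rounded up to 42.

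The stated figures reproduce closely enough. The point does not depend on an error in them.

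**2. Expected mix.** The article says "64 patients are offered treatment packages annually (40 SP and 24 AvPD". Assuming this carries over, 42 × 24/64 = 15.75, about 16 AvPD, and 42 × 40/64 = 26.25, about 26 SP.

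**3. Chance imbalance.** Let X be the number of AvPD patients in one arm, with 21 per arm and allocation that ignores diagnosis. Then P(X = x) = C(16, x) × C(26, 21 − x) / C(42, 21), centred on 8.

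| AvPD split | Difference in AvPD share | Probability of this or worse |
|---|---|---|
| 10:6 | 4/21 = 19 points | 0.341 |
| 11:5 | 6/21 = 29 points | 0.111 |
| 12:4 | 8/21 = 38 points | 0.025 |

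A split no worse than 9:7 therefore has probability 1 − 0.341 = 0.659.

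**4. What an imbalance does to the planned contrast.** Write a patient's change from T0 as (arm effect) + g × (1 if AvPD) + error, where g is the difference in *change* between the diagnoses. A constant level difference appears equally at T0 and afterwards, and cancels. The expected arm-by-time contrast, given the split, is

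true effect + g × (AvPD share in MCA − AvPD share in AAU).

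Two consequences follow. If g = 0, an imbalance does not shift the contrast. And a diagnosis main effect added to the repeated-measures model leaves the arm-by-time contrast unchanged, because it too is constant over time. Only a diagnosis-by-time term, or diagnosis as a covariate in a model of the follow-up score adjusted for baseline, can act on g.

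**5. Size of the shift.** The article gives no value for g. Assume 0.25 to 1.0 SD:

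- 10:6 split: 0.190 × 0.25 = 0.05 SD to 0.190 × 1.0 = 0.19 SD.
- 11:5 split: 0.286 × 0.25 = 0.07 SD to 0.286 × 1.0 = 0.29 SD.

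For scale only, with the SD of 2.754 the top of the range is 0.19 × 2.754 = 0.52 contemplation points for 10:6 (18% of 2.9) and 0.286 × 2.754 = 0.79 points for 11:5 (27% of 2.9).

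**6. Which outcomes are exposed.** Psychotherapy starts after T1 and URICA is not measured at T2, so therapy type cannot affect the primary outcome. LSAS, RSES and GSES at T2, and early attendance, are measured once patients are in diagnosis-specific groups.

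**The case against.** The strongest reply is that covariates belong in the SAP, which is announced but not shown, so the article cannot be faulted for leaving diagnosis out of a brief summary. That stands against any claim that diagnosis goes uncorrected. A reader might infer this from the article's silence, but the documents show only that no correction is stated. It does not remove the stratification choice, which the article itself fixes.

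Four other replies also stand:

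- Chance imbalance under valid randomisation adds variance and complicates interpretation; it does not bias the test.
- A reader might apply the diagnoses' level difference in severity directly to the arm comparison. The planned analysis uses baseline scores, so constant differences cancel and only differential change matters.
- A reader might argue that four sessions make up 29% of one programme (4/14) but 13% of the other (4/30). By T2 both groups have had four sessions of equal length; what differs is the type of therapy.
- The main objective is feasibility, and the acceptability and MCA-completion criteria are not between-arm comparisons.

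The article also gives grounds for pooling: the overlap is considerable and the dominant view is one spectrum. The entry label is only tentative, which may weaken it as a predictor. These points lower the likely value of g but do not show that it is zero.

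**Conclusion.** The point holds as a limited design weakness, not as a contradiction or a numerical error. Gender is the only named stratification factor in a trial that pools two diagnoses the article ties to severity and to different therapies. At 42 patients there is about a one-in-three chance of a 19-point or larger difference in AvPD share, and about one in nine of 29 points or more. These figures assume that the 40:24 mix carries over and that the arms are equal.

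The resulting shift would be 0.05 to 0.29 SD, but only if diagnoses differ in change by 0.25 to 1.0 SD, which is an assumption. It matters mainly for LSAS, RSES and GSES at T2 and for early attendance. It would be tempting to conclude that the primary result is confounded by programme. The documents do not support that, because therapy begins after T1. For URICA the concern is confined to the possibility that diagnosis itself predicts change in contemplation, for which the article gives no figure.

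**What to change.** Unless the SAP already does so, specify before unmasking:

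1. In the LSAS, RSES, GSES and URICA models, include the tentative diagnosis recorded before randomisation (SP or AvPD), either as a covariate in a baseline-adjusted model or as a diagnosis-by-time term. A diagnosis main effect alone is not enough (step 4 of the working).
2. State that this variable is fixed at its pre-randomisation value and that a diagnosis revised during MCA is never used. MCA is designed to verify or alter diagnoses, and diagnostic revision is itself an outcome, so the later diagnosis is affected by allocation.
3. Tabulate entry diagnosis by arm, and read the T2 and attendance results against that table.
4. Only if allocation is still open, stratify on entry diagnosis. Trial status expected the last inclusion in January 2023, so this is probably no longer possible.

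The cost is about one degree of freedom per contrast, with no new data, visits or patients. The gain will be small if diagnosis does not predict change.

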**Fig. 1 Fig1:**
[figure not shown]
CONSORT 2010 flow diagram

**Fig. 2 Fig2:**
[figure not shown]
Flow diagram of the intervention

### Setting

The setting of the study is Psychiatry South in Region Zealand, which is a rural region with several medium-sized cities, according to Danish standards. Three of these cities have psychiatric outpatient clinics (Maribo, Slagelse, and Naestved), which carry out psychotherapeutic treatment of patients with emotional disorders too serious to be managed by family doctors and primary sector psychologists and psychiatrists. Patients are typically referred by general practitioners, when they have failed to respond to one or two different treatments (medication and/or psychotherapy). The services in these clinics are covered by Danish public health insurance and involve both psychotherapy and psychopharmacological treatment (see also the “Introduction and rationale” section).

### Participants and eligibility criteria

We aim to include 42 patients who satisfy the inclusion criteria: (1) a patient with a tentative ICD-10 diagnosis of either SP or AvPD, (2) who is going to be offered treatment in the aforementioned clinics, (3) is 18–65 years of age, (4) has given written consent to participate, and (5) has sufficient knowledge of the Danish language.

Patients will be excluded if (1) the risk of suicide is high or moderate according to the investigator, (2) they have alcohol or drug dependency, and (3) they have a co-occurring eating disorder with BMI < 18 or psychotic illness.

### Recruitment

In the first consultation at the psychiatric clinic, clinicians will evaluate if the patient is eligible for psychotherapeutic treatment and stipulate a clinical diagnosis. If patients are eligible for treatment in the clinic, they will be invited to an information meeting with the first author, where they will be provided with information about the project. Following this, they can give informed consent to participate.

### Randomization and blinding

Patients will be randomized 1:1 to either the MCA or AAU on an individual level. Allocation to experimental intervention or comparison intervention will be computer-generated using the software REDCap © [50].

Due to the nature of the intervention, neither participants nor the researcher who will administer the intervention can be blinded to allocation. However, data will be re-coded for concealment and analyzed without access to information about allocation. The conclusion will be written prior to unblinding.

### Experimental intervention

The MCA, as described in the “Introduction and rationale” section, will include the possible administration of the following nine assessment instruments:

### Present State Examination (PSE)

PSE is a semi-structured interview that seeks to provide an objective evaluation of symptoms associated with mental disorders. It consists of 140 items and is scored on a 3-point or 4-point scale [51].

### Structured Clinical Interview for DSM-5 (SCID-5)

SCID-5PD is a semi-structured interview guide for evaluation of the 10 DSM-5 Personality Disorders.

### The Examination of Anomalous Self-Experience (EASE)

EASE is a semi-structured checklist for clinical-phenomenological exploration of experiential disturbances. Scores are summed up in a *global score*, with five *sub-scores*: Cognition and stream of consciousness, Self-awareness and presence, Bodily experiences, Demarcation/transitivism, and Existential reorientation [52].

### The Screen for Cognitive Impairment in Psychiatry (SCIP)

SCIP is a neuropsychological test for quick and objective quantification of cognitive function in patients with psychiatric disorders. The Danish translation has demonstrated validity for the detection of objective cognitive impairment [53]. It assesses verbal learning and memory, delayed memory, working memory, word mobilization, and processing speed [54].

### Autism Diagnostic Observation Schedule (ADOS-2)

ADOS-2, module 4 [55], is a semi-structured and standardized observation of communication, social interaction, and creative use of materials used to assess autism spectrum disorder pathology.

### Wechsler Adult Intelligence Scale—Fourth Edition (WAIS-IV)

The WAIS is an IQ test designed to measure intelligence and cognitive ability in adults and older adolescents [56]**.**

### Conners’ Adult ADHD Rating Scales (CAARS)

The CAARS is a test developed to diagnose attention problems, such as ADHD and ADD. It provides both Self-Report and Observer Report Forms, permitting multimodal assessment of adults with attention problems [57].

### Level of Personality Functioning—Brief Form 2.0 (LPFS-BF)

LPFS-BF is a brief 12-item self-report inventory developed to assess levels of personality functioning, as defined in the alternative model for personality disorders in DSM-5 Section III. It measures impairment in personality functioning within the domains of self-functioning and interpersonal functioning [58].

### Personality Inventory for DSM-5, 36-item version (PID-36)

The PID-36 is an abbreviated version of the originally 100-item version of the Personality Inventory for DSM-5 (PID-5), which was developed to measure the pathological trait specifiers listed in the alternative model for personality disorders in DSM-5 Section III [59].

The instruments will be administered by the first author. No other clinicians or therapists will see the included patients in this period of time. Materials from the medical record and from the full MCA will be presented for case supervision with a senior psychiatrist, with the option of getting an additional opinion from another senior consultant in case of diagnostic uncertainty. This procedure is included in order to ensure solid diagnostic verification or alteration. Therapists and teams are informed of the results of the MCA, in order for them to use the extra information about the patient in the following psychotherapeutic intervention, which will be administered after completion of the primary endpoint.

